# Telehealth Care for Mothers and Infants to Improve the Continuum of Care: Protocol for a Quasi-Experimental Study

**DOI:** 10.2196/41586

**Published:** 2022-12-15

**Keywords:** telehealth care, continuum of care, maternal, newborn, and child health, portable health clinic, parenting, prenatal, pediatrics

## Abstract

**Background:**

Ensuring an appropriate continuum of care in maternal, newborn, and child health, as well as providing nutrition care, is challenging in remote areas. To make care accessible for mothers and infants, we developed a telehealth care system called *Portable Health Clinic for Maternal, Newborn, and Child Health*.

**Objective:**

Our study will examine the telehealth care system’s effectiveness in improving women’s and infants’ care uptake and detecting their health problems.

**Methods:**

A quasi-experimental study will be conducted in rural Bangladesh. Villages will be allocated to the intervention and control areas. Pregnant women (≥16 gestational weeks) will participate together with their infants and will be followed up 1 year after delivery or birth. The intervention will include regular health checkups via the Portable Health Clinic telehealth care system, which is equipped with a series of sensors and an information system that can triage participants’ health levels based on the results of their checkups. Women and infants will receive care 4 times during the antenatal period, thrice during the postnatal period, and twice during the motherhood and childhood periods. The outcomes will be participants’ health checkup coverage, gestational and neonatal complication rates, complementary feeding rates, and health-seeking behaviors. We will use a multilevel logistic regression and a generalized estimating equation to evaluate the intervention’s effectiveness.

**Results:**

Recruitment began in June 2020. As of June 2022, we have consented 295 mothers in the study. Data collection is expected to conclude in June 2024.

**Conclusions:**

Our new trial will show the effectiveness and extent of using a telehealth care system to ensure an appropriate continuum of care in maternal, newborn, and child health (from the antenatal period to the motherhood and childhood periods) and improve women’s and infants’ health status.

**Trial Registration:**

ISRCTN Registry ISRCTN44966621; https://www.isrctn.com/ISRCTN44966621

**International Registered Report Identifier (IRRID):**

DERR1-10.2196/41586

## Introduction

In Sustainable Development Goal 3, maternal, newborn, and child health (MNCH) were identified as essential issues for the world to address [1]. A vital and global framework in improving mothers’, newborns’, and children’s health status is ensuring the continuum of care in MNCH within resource-limited settings. The continuum of care is the series of care throughout the adolescence and prepregnancy periods, the antenatal period, and the motherhood and childhood periods. Further, in terms of the nature of care, the continuum of care spans across community care, primary care, and advanced care [2-4]. Comprehensively monitoring infants’ nutrition status has also been emphasized in the context of the continuum of care in MNCH [5]. To ensure infants’ physical and psychological development and long-term health, they must receive appropriate care at the right times.

In this context, telehealth care is gaining attention, as it can be used to fill the gaps in the continuum of care [6]. Telehealth care may have the potential to monitor and provide care for high-risk pregnancies [7,8]. According to previous studies, telehealth care provided through either the internet or the telephone for the treatment of postpartum depression showed favorable effects thereon (mean difference: −1.81, 95% CI −2.68 to −0.93) [9]. Further, by using telehealth care monitoring, women with gestational diabetes mellitus showed an improvement in hemoglobin A1c levels (−0.41%, 95% CI −0.25% to −0.04%) when compared with a control group [10]. Another study on gestational diabetes mellitus found lower incidence rates of cesarean sections and maternal and neonatal complications in the telehealth care group [11]. Thus, the need for telehealth care follow-ups is sure to gain importance in the future.

In Bangladesh, the MNCH status has been improving. However, the maternal and neonatal mortality rates in Bangladesh are still among the highest in Asia; 173 maternal deaths per 100,000 live births and 19.1 neonatal deaths per 1000 live births were reported in 2019 [12]. As a considerable number of maternal and neonatal deaths and gestational complications are avoidable through early health intervention, providing appropriate and continuous care is essential. However, only 44% of women receive antenatal care (≥4 times) from a medically trained health care provider, and 47% of women and 46% of newborns do not receive any postnatal care [13], indicating inadequate MNCH services in Bangladesh. Further, Bangladesh’s cesarean section rate (30.7%) [12], which is higher than the global mean, may be a consequence of insufficient health care, as the cesarean section rate is often considered a proxy indicator of women’s access to care. Several factors have been identified that relate to the lower utilization of MNCH care services, including family wealth, previous experiences of childbirth, autonomy in women [14], and the distance to health facilities [15]. Therefore, financially and physically affordable care needs to be explored further to improve access to care.

Infants’ development status has also been recognized as a problem in Bangladesh; 28% of newborns had a low birth weight in 2015 [16], which was the highest low birth weight rate among newborns in the world at the time. Accordingly, undernutrition in 5- to 9-year-old children was also reported, with 18% of children categorized as *thin* (BMI of <−2 SDs below the mean)—the third highest undernutrition rate among 5- to 9-year-old children in the world. Anemia was also detected among 43% of children aged 6 to 59 months [12]. Hence, children’s nutrition status is also an essential aspect that needs to be monitored at and after birth.

The Portable Health Clinic (PHC) is a telehealth care system that comprises a set of sensor devices in an attaché case and an information system that can automatically triage health levels once users input the results of a checkup [17]. Originally developed in collaboration with Grameen Communications and Kyushu University, the PHC has been used in Bangladesh for telehealth checkups with over 45,000 people to prevent lifestyle diseases, such as diabetes and hypertension. Receiving care at home is beneficial for people who live in remote areas where access to health care is limited. Later, the MNCH module—PHC for Maternal, Newborn, and Child Health (PHC-MNCH)—was developed and piloted in rural areas of Bangladesh to provide antenatal and postnatal health checkups [18,19]. The PHC-MNCH has been renewed, and its original coverage (16 gestational weeks to 6 weeks after birth) has been expanded to include follow-ups at 1 year after birth for perinatal complications and infants’ health and nutrition status (ie, through home visit services).

Our study thus examines the effectiveness of a telehealth care intervention for improving women’s and infants’ care uptake in rural areas of Bangladesh. Additionally, it examines the effectiveness of telehealth care in detecting health problems among women and infants.

## Methods

### Study Design and Sites

Our study is quasi-experimental, and it will be conducted in 6 villages within the Chhaygaon Union of Bhedarganj Upazila (subdistrict), Shariatpur District, Bangladesh (Figure 1; trial registration number: ISRCTN44966621). Located approximately 80 km from Dhaka, these villages are in the suburb of the capital. Among the nine villages in the Chhaygaon Union, the East Chhaygaon, Middle Chhaygaon, and Lakarta villages were purposively set as the intervention cluster, and the Gangshar, Nazimpur, and Aterpara villages were set as the control cluster. The villages were allocated to the intervention and control areas such that the population sizes (intervention area: N=6378; control area: N=6178), geographic locations of the villages, and access to health facilities (each area has a health facility) were similar between the two areas. In the intervention arm, we conducted a pilot study in which we used the PHC system between June 2019 and May 2020 to follow women and infants from 16 gestational weeks to only 6 weeks post partum, with a shorter postpartum follow-up period than the one described herein.

**Figure 1 figure1:**
[figure not shown]
(A) Project site villages within the Chhaygaon Union of Shariatpur District. Among the nine villages, the six that are not bracketed are the study sites. (B) The location of Shariatpur District in Bangladesh.

### Study Population and Selection Criteria

A flow diagram of participants for the enrollment, allocation, follow-up, and analysis stages is presented in Figure 2. Different selection criteria will be applied to intervention, baseline survey, and end line survey participants. The inclusion criteria for intervention participants are (1) women at reproductive age (between 15 and 49 years), (2) women at ≥16 gestational weeks, and (3) women living in intervention villages at the time of enrollment. After birth, their infants will also be enrolled in the intervention cluster.

Baseline survey participants will be women in the intervention and control clusters who experienced giving birth between June 2015 and May 2019 (ie, before the pilot study). End line survey participants will be women in the intervention and control clusters who give birth between November 2020 and October 2024. Women who experience a miscarriage or a stillbirth during this period will also be included as participants.

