### Recruitment and Consent of Participants

All eligible women living in the intervention villages will be recruited for the study intervention. Local informants will collect information about eligible women from local citizens every month in all of the intervention cluster villages by visiting resident reproductive-age women individually. For women who might be pregnant, a test kit will be provided to confirm their pregnancy status. The expected recruitment period for intervention participants is June 2020 to June 2024. Baseline survey participants will be recruited based on information regarding their past pregnancy experiences, which will be obtained through the local informants and individual home visits.

We will explain the study purpose to potential participants, and their consent will be indicated by their participation in the intervention study or the questionnaire surveys. Their participation will be voluntary, and they will be free to join or withdraw at any time.

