#### Health Checkup

We will collect the health checkup data of intervention cluster participants throughout the intervention to identify gestational and maternal complication symptoms and health problems. The health checkups will be conducted during 9 home visits, which will be scheduled at approximately 16, 24, 32, and 36 weeks of gestational age and at approximately 2 to 3 days, 7 days, 6 weeks, 6 months, and 12 months after delivery or birth. The measurement- and interview-based checkup items are presented in Textboxes 1 and 2. Health statuses will be categorized into 4 levels according to the criteria developed by Japanese and Bengali obstetricians and medical professionals. Excerpts of criteria details are presented in Multimedia Appendix 3.

With regard to the control cluster, we will not collect health checkup biometric data. This is because conducting health checkups in the control area may affect the mothers’ awareness of health-seeking behaviors and result in bias in the intervention results.

Health checkup items for mothers at different periods.

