### Study Outcomes and Measurements

The following outcomes will be compared based on the baseline and end line surveys: the frequency of antenatal and postnatal care visits by health care providers conducted through health checkups with the PHC or at health facilities; the detection rate of gestational complication symptoms (suspected gestational diabetes, pregnancy-induced hypertension, anemia, preterm birth, and postterm birth); the detection rate for neonates and infants with suspected jaundice, anemia, and growth delay; the percentage of infants who started complementary feeding at 6 months after birth; and the percentage of participants who sought health care or exhibited health-seeking behaviors or self-care behaviors upon experiencing health problems.

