### Participants’ Timelines

The details of participants’ timelines are described in Multimedia Appendix 4. Women will be enrolled at approximately 16 gestational weeks, that is, when they receive the first antenatal checkup. They will be followed up at 9 points in time via health checkups. Infants will be enrolled at birth and followed up at 5 points in time after birth.

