## Results

Recruitment began in June 2020, and it is expected to continue until June 2024. We consented 295 mothers in the study by June 2022. Data cleaning and analysis will begin after the data collection is complete.

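### The June 2024 end of data collection cannot be squared with an end line cohort of births to October 2024 or with follow-up to one year after birth

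*Protocol article*

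**What the plan says.** The end line cohort is set in Study Population and Selection Criteria: "End line survey participants will be women in the intervention and control clusters who give birth between November 2020 and October 2024". Under Data Collection Methods and Evaluation, the effect of the intervention is judged by comparing the areas on the baseline and end line questionnaires, so this cohort carries the main comparison.

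The other dates and time points are:

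- **End of data collection** (Abstract, Results): "Data collection is expected to conclude in June 2024".
- **Recruitment** (Recruitment and Consent of Participants): "The expected recruitment period for intervention participants is June 2020 to June 2024". The main Results section repeats it: "Recruitment began in June 2020, and it is expected to continue until June 2024".
- **Length of follow-up** (Abstract, Methods): participants "will be followed up 1 year after delivery or birth". The Interventions section gives the same span.
- **Last home visits** (Health Checkup): "6 weeks, 6 months, and 12 months after delivery or birth". These checkups are made in the intervention area only.
- **Gestational age at entry** (Participants' Timelines): "Women will be enrolled at approximately 16 gestational weeks".
- **A compared outcome tied to infant age** (Study Outcomes and Measurements): "the percentage of infants who started complementary feeding at 6 months after birth".

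The main Results section adds that cleaning and analysis start only once data collection is over.

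**The concern.** A cohort whose births run to October 2024 cannot be fully observed by a data collection that stops in June 2024. Women who deliver from July to October 2024 belong to the cohort but have not given birth when collection ends. Infants born in the months before that are too young for the 6-month feeding outcome. Those born in the preceding year cannot have their 12-month visit.

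The stake is who is in the comparison. If the dates stand, someone must decide at the end which births count for which outcome, and the article gives no rule. A choice made late, or made differently in the two areas, can affect the contrast. There is a further, conditional risk. Ethics Approval says the control area receives the intervention once the study is complete. If completion is taken to be June 2024, control women who deliver from July to October 2024 could be exposed while still inside the comparison cohort.

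**Working it through.** **Inputs.** Birth window November 2020 to October 2024; recruitment June 2020 to June 2024; data collection to June 2024; entry at about 16 weeks; visits at 6 and 12 months; about 1000 eligible dyads (Sample Size). Two assumptions are mine: term at 40 weeks, so 24 weeks (168 days) from entry to delivery, and births spread evenly over the window.

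**Step 1: does the birth window follow from recruitment?**
- Start: 1 June 2020 + 168 days = 16 November 2020. This reproduces the stated November 2020 start.
- End: 31 October 2024 − 168 days = 16 May 2024. Women enrolled at 16 weeks up to then deliver inside the window.
- Overspill: 17 May to 30 June 2024 is 45 days, about 1.5 of 49 recruitment months (1.5/49 = 3%). A woman enrolled at 16 weeks on 30 June 2024 is due on 15 December 2024.

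The window is therefore recruitment shifted by about five months, with a small misfit at the far end.

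**Step 2: what end of data collection do the other dates require?**
- Last eligible birth + 12 months: October 2024 + 12 months = October 2025, which is 16 months after June 2024.
- Last enrolment at 16 weeks (30 June 2024) + 24 weeks + 12 months = mid-December 2025.

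The stated June 2024 is not reproduced by either route.

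**Step 3: share of the cohort affected if collection ends on 30 June 2024.** The window has 48 months. Share = birth months too late / 48.

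| Time point | Births too late | Months | Share | Of about 1000 dyads | Remaining |
|---|---|---|---|---|---|
| Birth itself | Jul–Oct 2024 | 4 | 8.3% | 83 | 917 |
| 6 months | Jan–Oct 2024 | 10 | 20.8% | 208 | 792 |
| 12 months | Jul 2023–Oct 2024 | 16 | 33.3% | 333 | 667 |

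The rows are cumulative: the later ones include the earlier. Counting days instead of months gives 8.4%, 20.9% and 33.4%. If collection ended on 1 June 2024, the day counts would be 10.4%, 22.9% and 35.4%.

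The dyad counts also assume that the figure of about 1000 refers to the whole birth window, which the article does not say. The 917 lies just under the stated recruitment minimum of 925, but that gap is within the rounding of an approximate 1000, so I put no weight on it.

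**Step 4: which shares bear on the comparison?**
- The 8% touches every end line outcome, because these births have not happened.
- The 21% touches complementary feeding at 6 months.
- The 33% touches completed one-year follow-up. The 12-month checkups are collected in the intervention area only, and Study Outcomes and Measurements fixes no compared outcome at 12 months. Infant anemia and growth delay are listed without an age.

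**The case against.** The strongest reply is that the conflict hangs on one sentence. June 2024 appears as the end of data collection only in the Abstract. The body uses the same month for the end of recruitment, and the main Results section gives no end date for data collection. The Abstract may simply have attached the wrong label to the recruitment date. If so, no data are lost and the repair is mainly one corrected sentence. The detailed participant timeline is in Multimedia Appendix 4, which is not at hand. This reading is plausible, and the match in Step 1 supports October 2024 as deliberate. It would explain the conflict, but the article as published still states dates that cannot all be met.

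Three stronger readings are tempting, and the article does not support them:

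- **A third of the comparison is lost.** The third applies to completed one-year follow-up. The compared outcomes come from a questionnaire whose timing after birth is not stated, and none is set at 12 months.
- **Recruitment to June 2024 contradicts the birth window.** It fits except for about the last six weeks of 16-week enrolments. Since eligibility is 16 weeks or later, some of those women would still deliver by October. What does stand is that recruiting until the month collection ends leaves the last women enrolled no follow-up.
- **Infants under 6 months will be counted in the feeding denominator.** The article does not define that denominator, and an analysis plan may do so.

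**Conclusion.** The point holds as an inconsistency of dates. The stated end of data collection is incompatible both with the birth window of the end line cohort and with the promised year of follow-up. If the Abstract is meant literally and births are even, 8% of the cohort is unobservable and 21% cannot have the 6-month feeding outcome. The antenatal care measure behind the sample size loses only the 8%. If the Abstract has mislabelled the end of recruitment, those losses vanish. What then remains is a wrong date, an unstated end of data collection, and a small group enrolled after about mid-May 2024 who receive the intervention but would mostly deliver outside the end line cohort. The article does not settle which reading is meant, so the sponsor has to say.

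**What to change.** State one consistent set of four dates: last enrolment, last eligible birth, end of follow-up and end of data collection.

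**If June 2024 is the end of recruitment:**
- Correct the Abstract and give an end of data collection that covers the last eligible birth plus the promised follow-up, about October 2025.
- Align the far end, either by closing 16-week enrolment by about mid-May 2024 or by extending the birth window to mid-December 2024 in both areas. The second choice moves the end of data collection to about December 2025.

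The cost is a correction to the article and registry, plus fieldwork to the stated end if it was not already planned.

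**If June 2024 is the end of data collection:**
- End the birth window and recruitment earlier. For all women enrolled at 16 weeks to deliver by 30 June 2024, enrolment must close by about 14 January 2024 (30 June 2024 − 168 days). A full year for everyone needs births to end in about June 2023 and enrolment to close about 168 days before that, in mid-January 2023. Otherwise, say that later participants have shorter follow-up.
- Set birth cut-offs by outcome, identically in both areas: about June 2024 for antenatal outcomes and December 2023 for complementary feeding at 6 months.
- Restate the dyads available for each outcome.

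This needs no extra fieldwork. Its price is fewer dyads for the later outcomes: about 792 of 1000 for feeding, on the assumptions above.

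Under either option, fix the dates before end line collection starts, and tie the handover of the intervention to the control area to the same end date.

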**Figure 2 figure2:**
[figure not shown]
Flow diagram of participants for the enrollment, allocation, follow-up, and analysis stages.

### Recruitment and Consent of Participants

All eligible women living in the intervention villages will be recruited for the study intervention. Local informants will collect information about eligible women from local citizens every month in all of the intervention cluster villages by visiting resident reproductive-age women individually. For women who might be pregnant, a test kit will be provided to confirm their pregnancy status. The expected recruitment period for intervention participants is June 2020 to June 2024. Baseline survey participants will be recruited based on information regarding their past pregnancy experiences, which will be obtained through the local informants and individual home visits.

We will explain the study purpose to potential participants, and their consent will be indicated by their participation in the intervention study or the questionnaire surveys. Their participation will be voluntary, and they will be free to join or withdraw at any time.

### Interventions

We will conduct a telehealth care intervention for women (from pregnancy [at ≥16 gestational weeks] to 1 year after delivery) and their infants (from birth to 1 year of age). The content and processes of the interventions are detailed below.

